**FIGURE 2 F2:**
[figure not shown]
Flow chart of design and procedures.

After completion of all evaluation stages, workshops about sleep habits and the importance of sleep in childhood will be conducted by research team with teachers of the schools that participated in the study.

### Intervention With Serious Game “Perfect Bedroom: Learn to Sleep Well”

The serious game “Perfect Bedroom: learn to sleep well” will be the main resource used in this intervention, and was developed by [name] (Associate Professor at the Department of Psychology and on the Postgraduate Program in Psychobiology), [name] (Master’s Student on the Postgraduate Program in Psychology), and [name] (Student on Science and Technology). It is currently in process of patenting, registration number BR 10 2015 032215 1, and copyright has been registered in Brazil National Library Foundation, registration number 681. 074.

The game is based on sleep hygiene and includes a series of behavioral and environmental recommendations to promote healthy sleep, with the aim to teach and promote good sleep habits for children. In this regard, our serious game provides explanations about sleep hygiene habits, presenting them in a playful way, to make it more interesting for children. It includes the challenge of mounting a “perfect bedroom” based on the application of knowledge of healthy sleep habits.

Serious games such as this are composed by four components: boards, cards, bank notes and objects (**Figure 3**). First, to indicate adequate and inadequate sleep habits, cards with recommendations of sleep hygiene and additional explication about importance or consequences of do or not do this action (e.g., You do physical activity and play before bedtime. Playing next to bedtime will leave you agitated and sleepless) will be used. These cards also have indications of rewards for good sleep habits, that will be paid in Sleep Perfect’s bank notes. On the other hand, when cards have inadequate sleep habits no rewards will be given.

**FIGURE 3 F3:**
[figure not shown]
Components of serious game “Perfect Bedroom: learn to sleep well.” Copyright registered in Brazil National Library Foundation, registration number 681. 074.

Indicative phrases of adequate and inadequate sleep habits were elaborated according to findings in Allen et al. (2016) and Mindell et al. (2009). In this first research, evidences of common sleep recommendations were investigated to promote healthy sleep in children, identifying strong empirical evidences to support schedules and bedtime routines; limited access to electronics before bedtime and in bedroom; and independence to fall asleep at bedtime and when waking up at night. Moderated or limited evidences were found about: consistency in daytime routine; environment and conditions of bedroom (e.g., quiet, dark and with comfortable bed); or eating habits (e.g., to limit caffeine consumption; not to go sleep hungry; eat a healthy balanced diet) (Allen et al., 2016).

Another study that we used examined association between sleep hygiene and how well children sleep (Mindell et al., 2009). This choice was based on the key issue that it is essential to understand the relationship between adequate sleep habits and sleep patterns to propose interventions in habits that influence sleep. Thus, in school-aged children, target population of this protocol, significant associations were verified between presence of parents in bedroom, late bedtime, consumption of caffeine, television in bedroom and reduced total sleep times and more night waking. Thus, the research team selected recommendations according to empirical evidence of sleep hygiene practices that could promote healthy sleep.

The second component of the serious game are four boards representing the floor of the bedroom that the children will assemble. In addition, to be more interesting and dynamic we included bonus cards (e.g., Congratulations, you do not use your cell phone before bedtime. Take out two more Perfect Bedroom Cards!) and surprise cards (e.g., You have television and computer in your room. These objects hinder the beginning of sleep! Pass the turn!). To allow the players to buy the items that will compose the bedroom bank notes with values of 1 and 2 were created. Available for the children to buy with the notes are 32 objects, divided in eight types (lamp, pillow, bed, chair, window, table, wardrobe, and fan), with four different colors (pink, yellow, green, and blue), to assemble the ‘perfect bedroom’ without electronics devices. The last pieces of the game are cards that list the objects that can be purchased and their values.

To play, all participants will receive the necessary materials described, with the starting player randomly chosen. The first participant will draw a card from the perfect room cards deck, which contains adequate (positive cards) and inadequate (negative cards) sleep habits, bonus or surprise cards. After drawing one card the player must do the card indicates. The player who wins is the one who assembles the perfect room first, with all the items on the list, or the one with the most objects in their board.

The intervention will be conducted by three previously trained researchers. It will occur at the children’s school, twice a week (on Tuesdays and Thursdays), starting at 02:00 pm, for 3 weeks in a row, resulting in six sessions of 50 min each. In each session players will be challenged to set up the “perfect bedroom.” They will apply the behavioral and environmental changes of sleep hygiene to promote healthy sleep.

### Ethics Statement

This study was approved by the Research Ethics Committee of the Federal University of Rio Grande do Norte, Brazil (registration number 62016916.2.0000.5537). All participants (children and parents/guardians) will be volunteers and will provide written informed consent to their participation in the study. The study was conducted in conformity with the ethical standards proposed in the World Medical Association Declaration of Helsinki. In addition, the control group will receive the intervention after all evaluation stages.

### Proposed Analysis

The software IBM (Statistical Package for the Social Sciences [SPSS], 1968), version 21.0 will be employed for data analysis, assigning the 5% significance level for all statistical tests. The Kolmogorov–Smirnov (KS) Test will be used to verify normality. Inferential and descriptive statistics will be used to test hypothesis.

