## Abstract

Promoting a healthy sleep is a big challenge and becomes a strategic priority in public health, due to the severe consequences on children’s development and risk to psychiatric diseases. Interventions that promote healthy sleep, such as those that focus on the dissemination of behavioral and environmental recommendations of sleep hygiene with children, are presented as an alternative. Serious game design offers wide-reaching domains in health applications and is increasing in popularity, particularly with children and teens because of it’s potential to engage and motivate players differently from other interventions. This study aims to evaluate effects of serious game on sleep hygiene recommendations “Perfect Bedroom: learn to sleep well,” on sleep habits and sleep parameters of healthy children. This is an experimental, prospective and quantitative study. We will randomize children in experimental (*n* = 88) and no intervention groups (*n* = 88). The experiment has four stages (pre-intervention, intervention, post-intervention, and follow-up), which will count with participation of children and their parents/guardians. In the evaluation stages, the guardians will answer questionnaires and scales to assess sociodemographic and health data, sleep habits and sleep pattern of their child. The children themselves will answer the following: a scale to assess sleepiness levels, a questionnaire to evaluate the serious game and the game itself, will characterize their bedroom and the activities they perform before sleep, with strategies developed by researches. Intervention with experimental group conducted with the serious game “Perfect Bedroom” will happen twice a week, for 3 weeks in a row, resulting in six sessions of 50 min each. Inferential analysis will be conducted for comparisons between groups and intragroups to measure effect of intervention in primary outcomes (sleep habits) and secondary outcomes (sleep parameters). We expect that the intervention with this game can provide valuable evidence to a new approach in promoting healthy sleep habits, with applications in clinical, educational, and familiar settings, which could diminish future health issues and risk at psychiatric diseases, decreasing the social burden of treatments for these conditions in children.

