#### UNESP Sleep Habits and Hygiene Scale (Child Version)

This scale contain 16 questions and will be used to evaluate characteristics of children’s sleep, according to four indicators that are considered causal to sleep hygiene: sleep routine (activities realized before bedtime); physiological alert (diurnal habits that would promote excitement or physical discomfort near to bedtime); cognitive/emotional aspects (indicators of emotional regulation and wellbeing before bedtime) and sleep environment (adequate sleeping environment in terms of temperature, comfort, and organization) (Pires et al., 2012). Each item is assessed on a five point of frequency scale from “never – no day” to “always – every day.” Furthermore, the scale contains five questions to evaluate bedtime resistance and daytime somnolence, assessed also on a five-point scale of frequency. Higher scores indicate worst habits of sleep hygiene. This has been empirically validated for use in Brazil.

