## Stepwise Procedures

### Participants

This study aims to recruit 176 healthy children enrolled in two private schools from Natal (Rio Grande do Norte – Brazil), as the number of children per class in these educational institutions ranges from 23 to 28. Schools will be selected by convenience, as there are difficulties to promote parental and school involvement (Jones et al., 2013; Wilson et al., 2014; Mindell et al., 2016), due to the concern of staff and parents about the activities developed in school and the necessity to adjust the research schedule to that of school activities, such as evaluation periods, vacation, science fair or school games. Furthermore, sample size was carried out using G^∗^Power 3.1.9, with alpha level of 5%, effect size of 0.5, and power of 95% for the two groups (Faul et al., 2007; Aberson, 2015). Results from this analysis indicated 88 participants to each group.

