### Design and Procedures

It will be used an experimental, prospective, quantitative and randomized controlled trial to compare effects of game application on change of habits and parameters of sleep, besides what the users will be able to do by playing this serious game. In order to achieve that, the following steps will be conducted: (1) randomization of participants to allocate each one in experimental or control group; (2) use of a control group that should not be submitted to intervention, to infer highest internal validity; (3) intervention with experimental group, which will allow us to evaluate if there was any modification in the parameters evaluated, determining the validity of the intervention and (4) evaluation of participants at three distinct moments throughout the study, namely: pre-intervention, immediate post-intervention and follow-up assessment, after 4 weeks (Suresh, 2011).

After selecting the schools by convenience, experimental and control groups are selected by two processes of randomization. The first will select which classes will compose the experimental and control groups in each school, throughout a basic method of randomization that is flipping a coin; in other words, one situation will be associated with each side of coin (e.g., heads – control and tails – experimental) to determinate the assignment of each class. Second, the function “Randomly assign subjects to groups” in online software GraphPad^1^ will be used to allocate participants of each class with valid data for analysis to each group.

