### Intergroup and Intragroups Analysis

Once confirmed that the groups did not present significative differences, the comparison procedure will be conducted. Variables included in sleep patterns (sleep latency, sleep efficiency, sleep and waking up times, total sleep time), sleep hygiene and sleep problems will be considered dependent variables and will be compared between experimental and control groups, during the three points in time where they will be evaluated, using independent student’s *t*-test and chi-square (χ^2^) with odds ratio and dimension of association (Phi and Cramer’s V), depending on the nature of the data. It will allow us to identify if the intervention with the serious game yielded improvements in objective sleep measures and sleep hygiene.

To evaluate possible improvements intragroup, comparisons will be conducted using: ANOVA (F) for repeated measures with Bonferroni’s post test and Q Chochran test. For all numeric variables percentage will be calculated with delta differences (post-test score minus the pre-test score) and percentage’s change [(post-test score) minus (pre-test score) divided by (pre-test score) multiplied by 100]. These measures will allow us to evaluate the intervention’s immediate effects and the maintenance of this effect after 4 weeks.

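### The primary outcome is an undivided domain tested at an unadjusted 5% at two post-baseline times, so the primary claim's false-positive risk exceeds 5%

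*Protocol article*

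**What the plan says.** The Abstract ranks the outcomes by domain: "primary outcomes (sleep habits) and secondary outcomes (sleep parameters". Neither it nor the later sections reduce the primary domain to one variable or one assessment.

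Several instruments could speak to sleep habits:
- The UNESP scale has 16 questions, scored "according to four indicators that are considered causal to sleep hygiene", plus five further questions on bedtime resistance and daytime somnolence.
- The bedroom sticker task and the pre-sleep activity sticker task match the second hypothesis in the Introduction, on sleep environment and pre-sleep activities.
- The first hypothesis there concerns irregular sleep and wake times, which the analysis section lists under sleep patterns. The line between primary and secondary is therefore not sharp.

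Assessments are at "pre-intervention, immediate post-intervention and follow-up assessment, after 4 weeks" (Design and Procedures). Under Intergroup and Intragroups Analysis, the dependent variables are "Variables included in sleep patterns (sleep latency, sleep efficiency, sleep and waking up times, total sleep time), sleep hygiene and sleep problems". They are to be "compared between experimental and control groups, during the three points in time where they will be evaluated", by t-test or chi-square. Proposed Analysis sets the threshold: "assigning the 5% significance level for all statistical tests". Bonferroni is mentioned only as the post-test of the within-group repeated-measures ANOVA.

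The sample size was computed "with alpha level of 5%, effect size of 0.5, and power of 95% for the two groups", and "Results from this analysis indicated 88 participants to each group". That calculation has one alpha, one effect size and two groups, so it describes a single comparison.

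**The concern.** The evidence for the game rests on the comparison between randomised arms. If several habit measures and two post-baseline times are each tested at 5%, and none is declared decisive beforehand, a positive conclusion can rest on the one that happens to cross the threshold. The chance of a false claim is then above the 5% used in the sample size calculation, and a reader of the results could not tell how far above. The Bonferroni post-test does not help, because it adjusts comparisons between times within an arm and not comparisons between arms.

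**Working it through.** **1. The plan's own figure.** Inputs from Participants: alpha 5%, effect size 0.5, power 95%, two equal groups.
- One-sided 5%, exact t: 88 per group, power 95.1%. The stated 88 is reproduced.
- Two-sided 5%, exact t: 105 per group. At 88 per group, power is 91.0%.

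The document does not state sidedness. For the present point it is enough that 88 is the answer to one test at 5%.

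**2. Counting tests.** Only the two post-baseline times are counted, since a baseline difference is not an efficacy claim.
- Narrow reading of the primary domain: hygiene scale only, 1 × 2 = 2 tests.
- Wider reading: hygiene scale, bedroom task and activity task, one summary each, 3 × 2 = 6 tests.
- All seven variables listed for the between-group analysis (latency, efficiency, sleep time, wake time, total sleep time, hygiene, sleep problems): 7 × 2 = 14 tests. Design and Procedures mentions the sleep disturbance scale only at pre-intervention. If it is not repeated, 6 × 2 = 12 tests.

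**3. Chance of at least one false positive.** With k independent tests at 5% and no true effect, this is 1 − 0.95^k.

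| Family | k | Independent | With assumed correlation |
|---|---|---|---|
| Primary, hygiene scale only | 2 | 1 − 0.95^2 = 9.75% | about 8% to 9% |
| Primary, with both sticker tasks | 6 | 1 − 0.95^6 = 26.5% | about 20% to 25% |
| Primary and secondary, sleep problems not repeated | 12 | 1 − 0.95^12 = 46.0% | about 32% to 43% |
| Primary and secondary, all seven variables | 14 | 1 − 0.95^14 = 51.2% | about 36% to 49% |

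The last column comes from simulating correlated normal test statistics (200,000 draws, two-sided 5%). The correlations are assumptions, because the document gives none: 0 to 0.5 between outcomes and 0.5 to 0.7 between the two times.

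**4. Effect of naming one primary test.** At 88 per group, effect size 0.5 and two-sided 5%, one test has an error rate of 5% and power of 91%. Testing the 4-week score only after a significant first test keeps the error rate for the pair at 5%. Splitting alpha over the two times instead (0.025 each) would give 85% power per test. These powers treat children as independent and assume all 88 per group are analysed.

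**The case against.** The strongest reply is that the Abstract does rank outcomes, and that only the hygiene variable in the between-group list is clearly a habit measure. Latency, efficiency and total sleep time are sleep parameters, hence secondary. The sticker tasks are analysed as learning outcomes of the game under a separate heading. The two times also have different roles, immediate effect and maintenance, and maintenance presupposes an effect to maintain. Finally, a condensed article may leave testing hierarchy to an analysis plan that is not shown.

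Much of this stands, and it limits the size of the problem. A reader might infer from the 14 tests that a chance effect is about as likely as not. The documents do not support that for the primary claim: 51% pools primary with secondary outcomes and counts a scale that may not be repeated. It also assumes independence, which is implausible when efficiency is computed from hours slept and the same children are measured twice. A reader might also multiply the 17 bedroom and 15 activity stickers by two times and expect about three chance findings (64 × 0.05 = 3.2). The document codes objects as present or absent but also plans totals, and it does not enumerate 64 between-arm item tests.

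The reply does not remove the point. Even the narrowest reading leaves two unadjusted tests and no decisive one. The ordering of immediate effect before maintenance is informal: nothing says the second test is made only if the first succeeds. Nor is this merely missing detail. The document states a rule of 5% for all tests, and an analysis plan that controlled multiplicity would have to depart from it.

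**Conclusion.** The concern holds in a limited form. As written, the primary claim has no single decisive test, and its between-arm comparisons are made at an unadjusted 5%. Assuming independence and no true effect, its false-positive risk is about 10% with the hygiene scale alone at two times. It is about 26% if the bedroom and activity tasks also count as habit measures, which is a reading supported by the Introduction's hypotheses and not a co-primary set that the document lists. Positive correlation lowers both figures, but under the assumed correlations they stay above 5%. For all seven listed variables, primary and secondary together, the figure is at most 46% to 51% (12 to 14 tests), or about 36% to 49% for 14 tests with the assumed correlations. That last range describes the whole set of results and should not be quoted as the error rate of the primary claim.

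**What to change.** Name one primary test. A workable choice is the UNESP hygiene score at the immediate post-intervention assessment, compared between arms at two-sided 5%. State that the score uses the 16 hygiene items and not the five further questions. Test the 4-week score at the same level only if the first test is significant.

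Restrict the sentence on 5% for all tests accordingly. Describe the secondary sleep parameters as supportive, or apply Holm's procedure across them; the supportive label is sufficient. Label sticker-item, subscale and within-arm tests as exploratory.

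The change is to wording and needs no extra children on the planned effect size (91% two-sided power at 88 per group, on the assumptions above). It has two costs. Secondary findings carry less weight or face a stricter threshold. The UNESP scale is parent-reported, so it is open to the social desirability that the article acknowledges under Anticipated Results, and only parents in the experimental arm attend the sleep workshop. If the authors judge that drawback too large, another single habit measure would serve equally well for error control.

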### Controlling for Covariates

To identify differences between experimental and control groups, which could invalidate the comparison procedure, inferential analyses in demographic and sleep variables will be conducted to test homogeneity. Adequate tests will be selected according to variable’s type and assumption or not of normal distribution of data in SW, as following:

(1) A Chi-square test (χ^2^) and generalized Fisher test will be used for categorical variables;(2) An independent student’s *t*-test (*t*) will be used for continuous variables.

### Intergroup and Intragroups Analysis

Once confirmed that the groups did not present significative differences, the comparison procedure will be conducted. Variables included in sleep patterns (sleep latency, sleep efficiency, sleep and waking up times, total sleep time), sleep hygiene and sleep problems will be considered dependent variables and will be compared between experimental and control groups, during the three points in time where they will be evaluated, using independent student’s *t*-test and chi-square (χ^2^) with odds ratio and dimension of association (Phi and Cramer’s V), depending on the nature of the data. It will allow us to identify if the intervention with the serious game yielded improvements in objective sleep measures and sleep hygiene.

To evaluate possible improvements intragroup, comparisons will be conducted using: ANOVA (F) for repeated measures with Bonferroni’s post test and Q Chochran test. For all numeric variables percentage will be calculated with delta differences (post-test score minus the pre-test score) and percentage’s change [(post-test score) minus (pre-test score) divided by (pre-test score) multiplied by 100]. These measures will allow us to evaluate the intervention’s immediate effects and the maintenance of this effect after 4 weeks.

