### Measures

#### Sociodemographic and Health Questionnaire

This questionnaire was designed to collect information about health, daily activities and demographic characteristics from parents and their children. It will be responded by parents and contains questions on:

(1) Child data: birth date; age; gender; grade level; potential sleep disorders, present or past; child’s medical and psychological condition; use of any medication or treatments; and additional activities of children.(2) Family data: job and education level of both parents, marital status, number of family members living with child and number of brothers/sisters.

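### The between-group outcome comparison is made conditional on non-significant baseline tests, a condition that correctly randomised groups will often fail by chance and for which no alternative is stated

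*Protocol article*

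**What the plan says.** Three statements in the protocol article combine into one rule.

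- Proposed Analysis sets the threshold: "assigning the 5% significance level for all statistical tests".
- Controlling for Covariates gives the purpose, "To identify differences between experimental and control groups, which could invalidate the comparison procedure", and the means, "inferential analyses in demographic and sleep variables will be conducted to test homogeneity". The tools named are chi-square, Fisher and independent t-tests. Despite its heading, the section adjusts for no covariate.
- Intergroup and Intragroups Analysis opens with the condition: "Once confirmed that the groups did not present significative differences, the comparison procedure will be conducted". It then names unadjusted t-tests and chi-square tests between arms at each of the three assessments, and repeated-measures ANOVA and Cochran's Q within arms. Changes and percentage changes from baseline are to be calculated, but no between-group test of them is named.

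No section gives a route for the case in which a baseline test is significant. Design and Procedures says that the arms are formed by randomisation.

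**The concern.** When arms are formed by randomisation, a baseline difference is a chance event. It does not invalidate the comparison, because the error rate of the outcome test already allows for it. The rule nevertheless lets any such difference stand in the way of the comparison, which includes sleep habits, the primary outcome named in the Abstract.

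Two things are at stake. If a baseline test is significant, the team has no planned analysis and must choose one after seeing data. If no test is significant, the arms are treated as equivalent. A non-significant result does not show that, and whatever imbalance is present passes into unadjusted tests.

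**Working it through.** **Inputs**

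- Level of each baseline test: 0.05 (Proposed Analysis). No multiplicity adjustment is stated for these tests.
- Sleep variables: seven. Intergroup and Intragroups Analysis lists "sleep latency, sleep efficiency, sleep and waking up times, total sleep time), sleep hygiene and sleep problems will be considered dependent variables". Counting sleep time and waking time separately gives five pattern variables, and one score each for hygiene and problems makes seven. Subscales would add more.
- Demographic variables: the Sociodemographic and Health Questionnaire collects, for the child, "birth date; age; gender; grade level" and, for the family, "job and education level of both parents, marital status, number of family members living with child and number of brothers/sisters". The Socioeconomic Status Questionnaire adds economic class. That is at least eight usable items.
- Number of tests, k: not stated. I assume 7 (sleep variables only) to 15 (7 + 8), with 5 and 20 as outer values.
- Group size: 88 per arm (Participants).

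**The plan's own figure**

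The plan gives no figure for the baseline tests, so the only one to reproduce is the sample size. With effect size 0.5, alpha 5% and power 95%, an exact t calculation gives 88 per arm one-sided (power 0.951) and 105 two-sided. So 88 reproduces as a one-sided calculation. The point made here does not depend on this; 88 is used only in the last step.

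**Chance of failing when randomisation is correct**

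For k independent tests, P(at least one p < 0.05) = 1 − 0.95^k:

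- k = 5: 1 − 0.774 = 0.226
- k = 7: 1 − 0.698 = 0.302
- k = 10: 1 − 0.599 = 0.401
- k = 15: 1 − 0.463 = 0.537
- k = 20: 1 − 0.358 = 0.642

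The sleep variables overlap (sleep efficiency, for instance, is computed from hours slept), so independence overstates the rate. To allow for this, let z_j = √ρ·u + √(1−ρ)·e_j, with u and e_j independent standard normal, and count the draws in which any |z_j| > 1.96 (200,000 draws):

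| k | independent | ρ = 0.3 | ρ = 0.5 |
|---|---|---|---|
| 7 | 30.2% | 27.0% | 22.9% |
| 10 | 40.1% | 35.3% | 28.7% |
| 15 | 53.7% | 45.9% | 36.0% |
| 20 | 64.2% | 54.2% | 41.9% |

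**What a pass leaves undetected**

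The largest standardised baseline difference that is still non-significant at 88 per arm is t(0.975; 174 df) × √(2/88) = 1.974 × 0.1508 = 0.298, or about 0.30 SD. Relative to the effect size of 0.5 used for planning, that is 0.298 / 0.5 = 0.60. The part of such a difference that carries into the outcome depends on the correlation between baseline and follow-up, which the document does not give. With fewer children analysed, the threshold rises above 0.30 SD.

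**The case against.** The strongest defence is that the opening sentence describes an order of work and not a bar. This is a condensed article, it says only that differences could invalidate the comparison, it does not say that every test must be non-significant, and the full plan might contain a fallback. Part of this stands. A reader might infer that the trial would then never have a primary analysis, and the text does not support that. The realistic harm is an analysis chosen after a significant baseline test has been seen. The between-group tests of the learning outcomes, under Evaluation of Serious Game, also carry no stated condition. But the conditional wording appears in one section and its rationale in another, so it is a written rule and not a detail left to a fuller document. A fallback elsewhere would have to reverse it.

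A second objection is that the null hypothesis of these tests is not strictly known to be true here. Materials and Equipment removes from the analysis children who miss the intervention, which can happen only in the experimental arm. Design and Procedures excludes children with missing data. Differences among those analysed can therefore reflect selection. This is correct, and it rules out the blanket claim that every baseline difference is chance. It does not rescue the condition: a significance test cannot tell selection from chance, and withholding the comparison repairs neither.

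A third objection is that baseline is not wholly ignored, since changes from baseline are calculated. That is only a partial answer, because the between-group tests named are unadjusted and none is assigned to the changes.

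A reader might also infer a much higher failure rate by adding clustering within school class. The documents do not support a figure: they give no intraclass correlation, and Design and Procedures is ambiguous on whether whole classes stay in one arm, because a coin flip by class is followed by random allocation of individual children.

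**Conclusion.** The point holds. As written, the between-group comparison is conditional on baseline tests at 5%, with no stated alternative. For 7 to 15 tests, correctly randomised groups would fail the condition in about 30% to 54% of trials under independence and about 23% to 46% with correlations of 0.3 to 0.5. These figures rest on an assumed number of tests, on assumed correlations, and on treating a single significant result as failure. Even the lowest value is close to one trial in four. Passing offers little reassurance, since differences of up to about 0.30 SD per variable go through unadjusted.

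**What to change.** In Intergroup and Intragroups Analysis, delete the condition and state that the between-group comparison will always be carried out. In Controlling for Covariates, replace the homogeneity tests with a descriptive table of baseline characteristics by arm.

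Replace the unadjusted between-group tests at the post-intervention and follow-up assessments with models that include the baseline value of the outcome: ANCOVA for continuous outcomes and logistic regression for binary ones. Any further covariates, such as school, age or socioeconomic class, are a matter of choice and should be named before outcome data are seen.

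The baseline measurements are already scheduled in the pre-intervention stage, so no new data are needed. The small cost is moving from simple tests to regression models and fixing the covariate list in advance.
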